## Abstract

**Background:**

Mindfulness-based and stress reduction interventions have been recommended by the National Institute for Health and Care Excellence guidelines in England and Wales as effective preventive mental well-being interventions for health care and other public sector staff at risk of poor mental health.

**Objective:**

This trial aims to assess the effectiveness of the increasingly implemented Mindfulness-Based Cognitive Therapy for Life (MBCT-L) intervention versus a routinely available Stress Reduction Psychoeducation (SRP) intervention in reducing perceived stress and improving other mental health and work-related outcomes in national health care and other public sector service employees.

**Methods:**

The trial is a multisite, single-blind, parallel-group, 2-arm superiority randomized controlled trial. Recruitment, interventions, and assessments will be conducted remotely via online platforms. We will recruit 260 health care and other public sector staff into 26 intervention groups across the United Kingdom, with the intervention delivered through human resource staff well-being provision channels affiliated with participating National Health Service trusts. Participants will be randomly allocated in a 1:1 ratio to either MBCT-L or SRP. Primary and secondary outcomes will be collected at 6, 12, and 20 weeks after randomization. The primary outcome will be the change in scores on the Perceived Stress Scale-14 from baseline to 20 weeks after randomization. Demographic, intervention-related, and health economic data will also be collected. Secondary outcomes will involve assessments of well-being, mental health state, and work-related engagement and performance. Adverse events will be recorded. Data analysis will involve multilevel modeling, and it will be conducted on an intention-to-treat basis. A substudy will involve online semistructured interviews after 20 weeks of randomization with a subsample of participants (n=30, 12%). Transcribed data will be subjected to thematic analysis to elicit qualitative outcomes on perceived well-being and work-related changes after intervention as well as drivers and barriers to intervention uptake and acceptability.

**Results:**

Recruitment of participants commenced on August 29, 2023. The target recruitment of 260 participants was reached on April 30, 2024. Follow-up outcome data collection was completed on September 30, 2024, and data analysis is underway. A total of 30 qualitative interviews have been conducted.

**Conclusions:**

Findings will inform future recommendations on intervention suitability and implementation for public care staff well-being.

**Trial Registration:**

International Standard Randomised Controlled Trial Number (ISRCTN) ISRCTN18049845; https://www.isrctn.com/ISRCTN18049845

**International Registered Report Identifier (IRRID):**

DERR1-10.2196/67695

## Introduction

### Background

Public sector employees present with higher levels of stress compared to those in other job sectors, with health care and public care staff, in particular, experiencing disproportionately high stress levels [1]. Stress levels in public sector employees have been further exacerbated by the COVID-19 pandemic, which has reportedly imposed additional stressors in the workplace, especially on health care staff [2-4]. In 2020-2021, stress, depression, or anxiety accounted for 50% of all work-related ill health, with the total number of cases of work-related stress, depression, or anxiety being 822,000, and a prevalence rate of 2480 per 100,000 employees in human health, social care, and education sectors in the United Kingdom [1]. Excessive stress and mental health problems, such as anxiety and depression, in public sector staff have also been broadly associated with further negative individual-level outcomes, such as burnout, compassion fatigue, and reduced quality of life and negative organizational outcomes, such as poor job satisfaction; presenteeism; and absenteeism and leaving work, including poor care provision [5-7]. Mindfulness-based training and stress management training are two approaches that have been recently recommended by the National Institute for Health and Care Excellence (NICE) [8] as effective psychotherapeutic interventions to be delivered in the United Kingdom in either online or face-to-face group modality to health care or other public care employees at risk of poor mental health.

While a broad range of organizational- and individual-level well-being interventions are currently being offered in National Health Service (NHS) trusts and other public sector workplaces, Stress Reduction Psychoeducation (SRP) is a standard usual care group program offered widely and in various formats across all geographic regions in England (United Kingdom) to health care staff as well as other public sector staff accessing psychotherapeutic interventions through their organizational well-being services affiliated with NHS trusts. Mindfulness-Based Cognitive Therapy for Life (MBCT-L) [9] is a newer, third-wave intervention, which is increasingly being implemented in the NHS and other public sector services. MBCT-L borrows its premises from the standard Mindfulness-Based Cognitive Therapy (MBCT) variant [10,11], which is a NICE-recommended treatment option for recurrent and mild to moderate acute depression [12], and is also included in clinical guidelines as a relapse prevention option in other countries [13-15]. Importantly, MBCT-L is an adaptation tailored to nonclinical populations and has been shown to be effective in improving well-being and mental health outcomes in various populations, including health care workers, as evidenced in previous work [16-20], including a recent randomized controlled trial (RCT) that showed moderate to large effects on health care staff well-being derived from MBCT-L compared to a waitlist control [21].

SRP and MBCT-L approaches are increasingly being implemented across the NHS trusts in the United Kingdom in online formats, particularly after the COVID-19 pandemic, in acknowledgment that digital modalities can overcome main barriers to intervention uptake and adherence [22]. However, MBCT-L is currently being offered as a workplace psychological program through the NHS trust’s well-being services in a limited number of trusts across the United Kingdom. Notably, MBCT-L is a longer-duration program, commonly lasting 8 or 9 weeks if a practice (retreat) day is included, as opposed to SRP, the duration of which can vary between 4 and 6 weeks. Furthermore, MBCT-L requires more skilled staff for its delivery, that is, specifically MBCT-trained staff, whereas SRP programs can be delivered by classically trained cognitive behavioral therapy practitioners, psychological well-being practitioners, or other health care staff trained in supporting people with common mental health problems in managing their conditions.

SRP and MBCT-L approaches differ in their conceptual and practical premises; while SRP relies on behavioral stress reduction techniques coupled with well-being and goal setting [23], MBCT-L is an enhanced approach that combines both stress reduction and cognitive therapy elements in one program, embedding mindfulness practices as well [9]. Thus, a presumed advantage of MBCT-L over SRP approaches is that the former teaches foundational coping skills that not only alleviate transient stress but also cultivate a long-term change in one’s attitude toward stress and promote a more positive outlook on stressful experiences and life more generally.

However, the 2 approaches have not yet been compared to one another in terms of their effectiveness as workplace interventions in improving stress and other well-being aspects and job-related outcomes. The findings of the review conducted by NICE in their recent guidance [8] indicated larger effects of face-to-face mindfulness-based approaches on stress and other mental health and job-related outcomes than stress reduction interventions in at-risk public sector populations. Moderate-quality evidence suggested that mindfulness-based approaches are effective in improving mental well-being; managing mental health symptoms; and decreasing absenteeism in public sector populations, including health care staff. Very-low-quality evidence suggested that such mindfulness interventions may improve job stress in such at-risk public sector populations. Furthermore, the reviewed mindfulness-based studies seemed to rely on mindfulness-based stress reduction approaches, largely without cognitive elements embedded, while some of the reviewed SRP studies included cognitive elements in their content and exercises. As for stress reduction approaches, moderate-quality evidence indicated that SRP was effective in improving job satisfaction; quality of life; and mental health literacy in targeted high-risk populations, including health care staff. Low-quality and very-low-quality evidence hinted that a stress management approach might be effective in improving stress and mental health symptoms in these populations.

### Study Rationale

The NICE review did not include any online mindfulness-based studies, while the included stress management interventions were delivered either face-to-face or online. All 5 mindfulness-based studies and all 5 stress management studies included in the NICE review had a waitlist or usual care as a comparator or no well-being comparator intervention. Only 1 of the stress management studies was based in the United Kingdom, while there were no other mindfulness-based studies that were conducted in the United Kingdom. Finally, while the NICE review consolidated some qualitative data assessing barriers and facilitators to intervention uptake, it only included 1 qualitative study, which involved another type of intervention, that is, digital cognitive behavioral therapy [8]. The findings of the study indicated that there are a number of positive aspects of the digital modality of such a well-being intervention, including convenience and discreteness or anonymity, while specific barriers (eg, time pressures) and drivers (eg, managerial support) were reported to impact engagement with the given intervention.

Therefore, in light of the lack of online mindfulness-based studies in the NICE review and a lack of studies directly comparing mindfulness-based and SRP approaches, the proposed superiority trial will assess the effectiveness and cost-effectiveness of the 2 approaches. Furthermore, in light of the lack of qualitative studies exploring the acceptability or effectiveness of either approach, this study aims to gather in-depth qualitative data from a subsample of participants to explore the perceived impact of the intervention, including postintervention changes in well-being and work performance, barriers and facilitators to the uptake and acceptability of such interventions, and their engagement throughout the program. The overarching research question is as follows: Does MBCT-L demonstrate superior efficacy to SRP in reducing perceived stress and improving mental health and work-related outcomes among public sector employees? The findings of this study are expected to fill in the aforementioned gaps in the existing research and are intended to inform the NHS and other public sector organizations on how to best invest in their future resource provision to retain and support their staff at risk of poor well-being.

## Methods

### Aim, Design, and Setting of the Study

#### Overview

The proposed Well at Work study is a single-blind, multisite, parallel-group, 2-arm superiority RCT that aims to assess the clinical effectiveness and cost-effectiveness of MBCT-L versus SRP in health care and other public sector staff who are seeking to access well-being support through human resource channels affiliated with the participating NHS trusts. The primary objective of this trial will be to determine whether there is a difference in change in the primary outcome on the Perceived Stress Scale-14 (PSS-14 [24]) between the 2 intervention groups from baseline to 20 weeks after randomization. The secondary objectives will be to assess the differences in change in any of the secondary mental well-being and work-related outcome measures between the 2 arms from baseline to each follow-up time point, that is, at 6, 12, and 20 weeks after randomization. Recruitment, interventions, and assessments will be conducted remotely via online platforms using videoconferencing and electronic technologies.

#### Qualitative Study

A substudy will involve online semistructured interviews to be conducted 20 weeks after randomization, with a subsample of participants from each arm gathering qualitative data for in-depth insights into participants’ perceived changes after intervention and their experiences and views in relation to intervention uptake and acceptability.

The Well at Work study is hosted by the University of Nottingham in the United Kingdom, which is the sponsor of the study, and will be mainly based across 4 public care (NHS) sites over 3 geographic regions in the United Kingdom, that is, Nottingham University Hospitals NHS Trust and Nottinghamshire Healthcare NHS Foundation Trust (the East of England); Sussex Partnership NHS Foundation Trust (South of England); and Tees, Esk and Wear Valleys NHS Foundation Trust (North of England). The online MBCT-L intervention will be offered across all 4 NHS trust sites, while 9 additional NHS trust sites will also be participating in the trial, namely Lincolnshire Partnership NHS Foundation Trust; Lincolnshire Community Health Services NHS Trust; Derbyshire Community Health Services NHS Foundation Trust; York and Scarborough Teaching Hospitals NHS Foundation Trust; South Tyneside and Sunderland NHS Foundation Trust; Leicestershire Partnership NHS Trust; Wrightington, Wigan and Leigh Teaching Hospitals NHS Foundation Trust; South West London and St George’s Mental Health NHS Trust; and Northern Care Alliance NHS Foundation Trust. These additional sites will be channeling interested staff to 1 of the 4 main NHS trust sites delivering the interventions. Given the online intervention delivery format, the trial aims, with this approach, to achieve wide geographic coverage and outreach across health care and other public sector staff in the United Kingdom seeking well-being support through their organizations, which is offered via the participating NHS trust sites.

#### Patient and Public Involvement and Engagement

A patient and public involvement and engagement (PPIE) group consisting of members of staff working in the public sector has been formed and consulted on the design of the study. The PPIE group is intended to provide input into all key aspects of the trial throughout its duration, from conceptualization to implementation, evaluation, and dissemination.

Reporting of the protocol is according to SPIRIT (Standard Protocol Items: Recommendations for Interventional Trials) guidelines (Multimedia Appendix 1).

### Sample Selection

Potential participants will be directed to the study through existing integrated care services; well-being hubs; and other human resource channels, which are accessed by staff working in health care and other public sectors, for example, social care and teaching, through the NHS trust sites participating in the trial. The communication of study information will be facilitated through a study flyer that will be circulated widely across the participating sites via email and other communication channels, including staff communication hubs; staff well-being websites; staff networks, newsletters, and social media (eg, Facebook [Meta Platforms, Inc] and X [X Corp]); and staff induction or other events.

Staff expressing an interest in the study will be directed to an online link facilitated via REDCap (Research Electronic Data Capture; Vanderbilt University) [25,26] tools hosted at the University of Nottingham, which will include a participant information sheet (PIS) with information about the study, followed by an eligibility screening form. The contact details of the study researchers will be provided in the PIS should any interested participants wish to ask any questions. Upon completion of the eligibility form, eligible participants will be emailed a link to a participant consent form on the REDCap platform. In the consent form, participants will also be asked to indicate whether they would be willing to receive information at a later stage about the qualitative substudy. Following the provision of informed consent on REDCap, participants will be directed on the platform to the survey containing the baseline assessment questionnaires. The inclusion and exclusion criteria are listed in Textbox 1.

Inclusion and exclusion criteria for the trial.
**Inclusion criteria**
Aged ≥18 yearsPart-time, full-time, honorary, or voluntary employment, seeking access to well-being support through one of the participating sitesCurrently working (ie, not on a sick leave)Having a competent command of the verbal and written English languageHaving access to a stable internet connection on a PC, laptop, or tablet
**Exclusion criteria**
Current diagnosis of a mental health condition from a general practitioner or mental health care professionalExperience of significant life events currently causing significant distressConcurrently attending or planning to attend a psychological or well-being intervention within the subsequent 3 months

### Screening

Exclusion criteria will be flagged up in the screening form, and interested participants deemed as ineligible will be contacted by the trial practitioner or facilitator team to verify their eligibility; if exclusion criteria are confirmed, interested participants will be signposted to alternative available support as appropriate, for example, to an MBCT for depression program run routinely at each involved site if participants experience high levels of depression. As this is the mechanism already in routine place for staff recruitment for these interventions through NHS trust well-being services, we will keep our exclusion criteria to the minimum.

### Sample Size

With reference to the trial’s primary outcome, 5 points on the PSS-14 will be considered as the minimum clinically important difference. Assuming a 2-tailed .05 significance level with 90% power (using analysis of covariance) and SD 7.7, a baseline and follow-up correlation of 0.2, and the correlation among follow-up measures of 0.7, a total of 76 participants will be needed to estimate the treatment effect from baseline at 20 weeks after randomization. Assuming the average group size is 8, the intraclass correlation coefficient is 15%, and the attrition rate is 25% (considering potential loss to follow-up), the final sample size was inflated to 208 participants to be randomly recruited in 26 groups (1:1 ratio) across all the recruitment sites. However, upon monitoring follow-up rates after approximately one-third of the participants were randomized, it was highlighted by a blinded independent statistician that the follow-up rate was approximately 62% and the group size was approximately 10. Therefore, the trial management group decided to update the sample size with 85% power to mitigate the loss to follow-up. A substantial amendment was submitted, and ethics approval was received for the sample size to be increased to 260 participants, divided across 26 groups.

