#### The MBCT-L Intervention

MBCT-L integrates conventional cognitive therapy techniques with stress reduction techniques and mindfulness practice, as in the original MBCT version, but has been adapted to apply to the general population as per established protocol [9]. The program includes 8 online weekly sessions lasting approximately 2 hours and an online practice day lasting approximately 6 hours. MBCT-L will run for 9 consecutive weeks or 10 weeks if a 1-week break is included (eg, due to school break or holidays) in a group-based format with an average of 8 participants recruited per group. The content includes themed teaching every week and guided meditation practices (eg, breathing practice and body scan), as well as everyday homework practices lasting 30 to 45 minutes. Participants will receive frequent automated text reminders about their upcoming sessions and homework or home practices via an automated text messaging service provided by a Generated Health system, Florence [27]. The program will be delivered by approximately 8 trained MBCT practitioners or facilitators across the main NHS trust sites, who are part of the teaching team involved in the MBCT-L interventions already being offered to public sector staff through the NHS trust services and have been trained under, and follow, the same MBCT training protocol [9].

The MBCT-L program broadly follows an overarching structure of developing mindfulness skills intended to enhance attentional control and awareness, cultivating a deeper understanding of how distress is created and maintained and how mindfulness training can address factors that contribute to its maintenance, learning skillful ways of relating to experience developed through awareness and practice, and learning to recognize unhelpful reactive patterns in everyday life and cultivate the capacity to respond to these with mindfulness and compassion. In the second part of the program, participants practice the application of this learning to everyday life, including work, to respond more effectively to stress and enjoy the positive aspects of life.

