#### Primary Outcome

The primary outcome will be the change in the PSS-14 [24] score from baseline to 20 weeks after randomization. The PSS-14 was selected as the primary outcome measure as it is a well-validated and internationally used self-report scale of perceived stress and has been widely used in previous trials assessing changes in stress levels in diverse populations, including public sector workers.

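### The 76 said to give 90% power at 20 weeks is the number for the mean of three follow-ups; the 20-week contrast needs 96

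*Protocol article*

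**What the plan says.** All figures are from the protocol article.

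- **Target difference** (Sample Size): "5 points on the PSS-14 will be considered as the minimum clinically important difference".
- **Error rates, method and SD** (Sample Size): "Assuming a 2-tailed .05 significance level with 90% power (using analysis of covariance) and SD 7.7".
- **Correlations** (Sample Size): "a baseline and follow-up correlation of 0.2" and "the correlation among follow-up measures of 0.7".
- **Result** (Sample Size): "a total of 76 participants will be needed to estimate the treatment effect from baseline at 20 weeks after randomization".
- **First inflation** (Sample Size): average group size 8, intraclass correlation 15% and attrition 25% lead to 208 participants in 26 groups.
- **Revision** (Sample Size): follow-up was found to be about 62% and group size about 10, after which "the trial management group decided to update the sample size with 85% power to mitigate the loss to follow-up". The new target is 260 in 26 groups.
- **Primary endpoint** (Primary Outcome): "The primary outcome will be the change in the PSS-14 [24] score from baseline to 20 weeks after randomization". The list of secondary measures treats the 6- and 12-week PSS-14 scores as secondary.
- **Analysis model** (Statistical Method): a multilevel model over the follow-ups that includes a follow-up by allocation interaction, so week 20 has its own treatment contrast.
- **Group size elsewhere** (The MBCT-L Intervention): "in a group-based format with an average of 8 participants recruited per group".

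**The concern.** A correlation among follow-up measures has no role in the sample size for a one-time-point ANCOVA. It enters when several follow-ups are averaged. Its presence among the inputs suggests that 76 was calculated for the mean of the three follow-ups and then described as the number for week 20.

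The two effects are different quantities. The average includes week 6, when MBCT-L, which runs for 9 or 10 weeks, cannot yet be complete. It also has smaller variance under the stated correlations. If the description is wrong, the published power belongs to an effect that is not the primary outcome, and a null result at 20 weeks would be read against a power that was never calculated for it.

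**Working it through.** **Inputs** (Sample Size): difference 5, SD 7.7, two-sided alpha 0.05, baseline–follow-up correlation 0.2, correlation among follow-ups 0.7. There are three follow-ups (weeks 6, 12 and 20) and 1:1 allocation.

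**Formula.** For ANCOVA on the mean of p follow-ups:

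- variance factor f = [1 + (p − 1) × 0.7]/p − 0.2²
- n per arm = 2 × (z₀.₉₇₅ + z_power)² × 7.7² × f / 5²
- (z₀.₉₇₅ + z_power)² is 10.507 at 90% power and 8.978 at 85%

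**Step 1: reproduce the plan's 76.** With p = 3, f = 2.4/3 − 0.04 = 0.76. Then n = 2 × 10.507 × 59.29 × 0.76/25 = 37.88, so 38 per arm and **76 in total**. The inflation follows: the design effect on 8 per group is 1 + 7 × 0.15 = 2.05, and 76 × 2.05/0.75 = 207.7, which is the plan's **208**. This also shows that the design effect was applied to the recruited group size, before attrition.

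**Step 2: the named endpoint.** With p = 1, f = 1 − 0.04 = 0.96.

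| Power | Mean of 3 follow-ups (f = 0.76) | Week 20 only (f = 0.96) |
|---|---|---|
| 90% | 37.88 → 38 per arm, 76 | 47.85 → 48 per arm, **96** |
| 85% | 32.37 → 33 per arm, 66 | 40.88 → 41 per arm, **82** |

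Other 20-week analyses at two-sided 0.05 and 90% power do not give 76 either: post-score only needs 100, and a raw change score needs 160.

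**Step 3: 20-week power with 76.** SE = 7.7 × √(0.96 × 4/76) = 1.731; 5/1.731 = 2.889; power = Φ(2.889 − 1.960) = **82.4%**. No clustering or attrition assumption is involved.

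**Step 4: 20-week power with 208.** The number analysed is 208 × 0.75 = 156.

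- Design effect on recruited size 8 (2.05): effective N = 156/2.05 = 76.1, power **82.4%**.
- Design effect on analysed size 8 × 0.75 = 6 (1 + 5 × 0.15 = 1.75): effective N = 156/1.75 = 89.1, power **87.9%**. Reaching 90% would take 96 × 1.75/0.75 = 224.

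**Step 5: 20-week power with 260.** The number analysed is 260 × 0.62 = 161.2. The 24 df are 26 groups minus 2.

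| Design effect on | Value | Effective N | SE | Power (normal) | Power (t, 24 df) |
|---|---|---|---|---|---|
| Recruited size 10 | 1 + 9 × 0.15 = 2.35 | 68.6 | 1.822 | **78.4%** | 75.0% |
| Analysed size 6.2 | 1 + 5.2 × 0.15 = 1.78 | 90.6 | 1.586 | **88.4%** | 85.7% |

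For 85% power at 20 weeks, the first convention needs 82 × 2.35/0.62 = 310.8, so 311. The second needs 82 × 1.78/0.62 = 235.4, so 236.

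**Step 6: where 260 may come from.** The article does not show its derivation. With the averaged-effect figure and the recruited-size convention, 66 × 2.35/0.62 = 250.2, so 251; 26 groups of 10 make 260. This is a plausible route, not a documented one.

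**The case against.** The strongest reply concerns the current target. A reader might infer that 260 is underpowered and that the stated 85% is false for week 20. The article does not support that. The 78% figure applies the design effect to everyone recruited, including the 38% without follow-up. With the roughly 6.2 per group who contribute data, power is 88% (86% on 24 df), and 236 participants would be enough for 85%. Because the article does not say how 260 was obtained, it cannot be shown that 260 inherits the error.

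A second reply is that the planned model uses all follow-ups, with multiple imputation under missing at random. With incomplete data, the 0.7 correlation lets weeks 6 and 12 inform the 20-week contrast. If everyone missing at week 20 had supplied both earlier visits, power with 260 would be about 87% even at group size 10. That pattern is optimistic and the article does not state it, but it means 78% is not a firm figure for the planned analysis.

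Both replies stand as far as 260 is concerned. Neither rescues 76. With complete data, the earlier visits add nothing to a separate 20-week contrast, and the 76 is quoted before attrition and clustering.

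It is also fair that 208 has been superseded and that recruitment and follow-up are complete, so the correction is to the text and not to the conduct of the trial.

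**Conclusion.** The statement that 76 participants give 90% power for the 20-week effect is wrong on the section's own inputs. The number is 96, a shortfall of 20 before inflation, and 76 gives about 82%. This rests only on the stated difference, SD, correlations, alpha and ANCOVA method.

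The 90% attached to 208 also fails for week 20 under either design-effect convention, by about 8 points on recruited size or about 2 points on analysed size.

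For 260, the supported conclusion is that 20-week power lies between about 75% and 88%, taking ICC 0.15 and 62% follow-up as given, and that the stated 85% is met or missed according to a convention the article leaves unnamed. The convention that reproduces 208 is the less favourable one, and partial follow-up data could raise its figure.

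The average of 8 per group in the MBCT-L section does not match 260/26 = 10. That is a separate, minor inconsistency and does not affect the calculations above.

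**What to change.** In the Sample Size section:

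1. Replace 76 with 96 at 90% power (82 at 85%) for the 20-week contrast, or state that 76 refers to the average treatment effect over weeks 6, 12 and 20.
2. Restate the 20-week power for 260 and name the design-effect convention: about 78% (75% on 24 df) on recruited size 10, or about 86–88% on analysed size 6.2. If credit is taken for partial follow-up data in the multilevel model, give the assumed pattern of missing visits.
3. Show how 260 was derived.

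Separately, reconcile the average group size in the MBCT-L section with 260 across 26 groups.

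The cost is a rewritten paragraph and possibly a less favourable published power. No further enrolment is needed, and the endpoint, model and analysis set do not change.
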